### 3.17 Are there any planned subgroup analyses?

For the primary objective we do not have subgroup analyses planned, but have considered possibilities. In the event that infant sex is not balanced we will use sex as a covariate. The potential subgroup analyses we have identified are measured skin color (pigmentation). These would only be explored in efforts to generate hypotheses and consequently to design future studies. Skin pigmentation is embedded in the design as infant skin color will be used as stratification criteria. Our objective measures of pigmentation could improve understanding the biological response to vitamin D.

## 4. Trial management

### 4.1 What are the arrangements for day to day management of the trial?

Refer to Table 2.

**Randomization:** Randomization will be set using RANDOMIZE.net which is a fee-for-service website. It enables randomization according to random block sizes, stratification, 2 treatment arms and verification of entry criteria; and will be used to track non-randomized infants (reference group).

**Data handling:** Two PhD trainees will be responsible for data entry including all screening data and data from visits. Data will be entered after each visit or as soon as when biochemistry data is available; our study co-ordinator (and registered nurse) will audit all of the data and communicate any abnormal findings to the study physicians ASAP. Any abnormal test will be repeated within 24 h and if still abnormal the child will move to standard of care (open label 400 IU/d) and be followed as intent-to-treat.

387 4.2 Describe the trial steering committee and if relevant the data safety and monitoring  
388 committee.

389 Since this trial uses vitamin D within amounts suitable for the general public we will not have a  
390 monitoring committee as required in the past [3]; see section 4.1 data handling above and  
391 **Diagram 2 and Table 3**. Each of the applicants will be a member of the steering committee and  
392 will meet prior to launching the study to review all procedures; then 6-monthly. The safety  
393 committee is comprised of a research nurse, the PI and 3 MDs who are co-applicants. We did not  
394 seek an arm's length safety officer since our dosages are  $\leq$  to the IOM UL. [name] can also  
395 advise if maternal vitamin D status is low.  
396

397 4.3 Describe any risks to the safety of participants involved in the trial.

398 The vitamin D dosages planned in this study are within the UL recommendations set for the  
399 general public by the IOM [19, 20] . We thus believe the risks associated with the interventions  
400 to be minimal. Nonetheless, we will monitor for status until 6 mo of age; the UL for vitamin D  
401 thereafter is higher at 1500 IU/d. The risks associated with blood sampling are minimized by  
402 small volumes. Lastly, dual-energy x-ray absorptiometry (DXA) scans are deemed minimal risk  
403 according to the International Society for Clinical Densitometry [21].  
404  
405  
406  
407  
408  
409  
410

411     Diagram 1: Randomization scheme

[figure not shown]

412  
413  
414  
415  
416  
417  
418  
419  
420  
421  
422  
423  
424  
425  
426  
427  
428  
429  
430

Diagram 2: Safety protocol - For use at inception 3, 6 and 12 months

[figure not shown]

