|                                             |                                                                                                                                                                                                                                                                                                                                                                                                                                                                                                                                                                                                                                  |       |      |      |       |
|---------------------------------------------|----------------------------------------------------------------------------------------------------------------------------------------------------------------------------------------------------------------------------------------------------------------------------------------------------------------------------------------------------------------------------------------------------------------------------------------------------------------------------------------------------------------------------------------------------------------------------------------------------------------------------------|-------|------|------|-------|
| 25(OH)D                                     | Safe range <225 nmol/L according to Canadian Paediatric Society (CPS) and using our in-house Liaison total 25(OH)D (Diasorin) to enable 24 h assessments. This assay may overestimate by up to 20% (1) and thus we have used the CPS guidelines here for safety assessments only. None of the infants in the previous trial (2, 3) had values above this if vitamin D dosage was ≤1200 IU/d and using LC-MS/MS analyses. If value exceeds this limit then review plasma and urine mineral concentrations and consider moving to standard of care based on physician assessment; if these are normal, then repeat sample in 3 mo. |       |      |      |       |

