| PTH                                         | Normal range 10-60 pg/ml. If value <10 or >60, PTH to be repeated with plasma and urine minerals. As long as these are within the normal range, follow as per study routine. If any mineral concentrations are abnormal as per the criteria defined below.                                                                                                                                                                                                                                                                                                                                                                       |       |      |      |       |
| Plasma Ca                                   | Normal range 2.2 –2.6 mmol/L. If value <2.0 or >2.6, repeat sample and include ionized Ca, P, and urine minerals. If total Ca <2.0 and ionized Ca <1.0, break study code. If total Ca >2.6 and ionized Ca > age specific 95% percentile and urine Ca:Cr >2.2, safety officers unblind the infant, move to standard of care and send for urgent endocrine assessment.                                                                                                                                                                                                                                                             |       |      |      |       |
| Ionized Ca                                  | Normal range for age using data from our previous trial (2, 3) which has been adopted by children's hospitals. If value is outside of 2.5 th to 97.5 th percentile range (see table below), sample to be repeated within 24 h. If repeated values are abnormal, safety officers to unblind that infant, move to standard of care or other appropriate action and potentially send for urgent endocrine assessment.                                                                                                                                                                                         |       |      |      |       |

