| Plasma phosphorus                           | Normal range for infants, 1.55-2.65 mmol/L. If <1.0 or >3.0, repeat with plasma Ca and urine mineral profile. If persistently abnormal, send for urgent endocrine/nephrology assessment.                                                                                                                                                                                                                                                                                                                                                                                                                                         |       |      |      |       |
| Urine Ca: creatinine                        | Urine Ca:cr >2.2 combined with total plasma Ca >2.6 and ionized plasma Ca >97.5 th percentile, safety officers to unblind as above for plasma Ca.                                                                                                                                                                                                                                                                                                                                                                                                                                                                     |       |      |      |       |
| Urine P: tubular reabsorption of phosphorus | Tubular reabsorption of phosphorus (TRP) normal: 85-100%. If concentration abnormal, verify with a repeat sample and assess serum mineral status. If plasma concentrations are normal, repeat in 3 months. If persistently low, unblind infant at this 3 month point.                                                                                                                                                                                                                                                                                                                                                            |       |      |      |       |

 Based on values currently used at the Montreal Children's, Shriners, CHEO and General Hospitals.

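### Section 4.1 moves every infant with a confirmed abnormal test to open-label 400 IU/d, while Table 3 states a different action for several analytes

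*Protocol*

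**What the plan says.** Protocol Section 4.1, under Data handling, gives a single rule: "Any abnormal test will be repeated within 24 h and if still abnormal the child will move to standard of care". It specifies open-label 400 IU/d, with follow-up as intent-to-treat. It does not define abnormal, cite Table 3 or exempt any analyte.

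Table 3 sets analyte-specific limits and actions:

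- **25(OH)D above 225 nmol/L:** review plasma and urine minerals, then "consider moving to standard of care based on physician assessment; if these are normal, then repeat sample in 3 mo".
- **PTH outside 10-60 pg/ml:** repeat with plasma and urine minerals. "As long as these are within the normal range, follow as per study routine". The row's last sentence, on abnormal minerals, breaks off without an action.
- **Plasma Ca, high side:** "If total Ca >2.6 and ionized Ca > age specific 95% percentile and urine Ca:Cr >2.2, safety officers unblind the infant", with a move to standard of care and urgent endocrine assessment.
- **Urine Ca:creatinine:** "Urine Ca:cr >2.2 combined with total plasma Ca >2.6 and ionized plasma Ca >97.5" (97.5th percentile) leads to the same unblinding.
- **Ionized Ca:** if outside the 2.5th to 97.5th "percentile range (see table below), sample to be repeated within 24 h". A confirmed abnormal value leads to unblinding and a move or other suitable action.
- **Plasma phosphorus below 1.0 or above 3.0 mmol/L:** repeat with other minerals, and refer urgently if the abnormality persists.
- **TRP outside 85-100%:** verify with a repeat sample, and repeat in 3 months if plasma values are normal. Unblind if it is still low then.

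Section 4.2 sends the reader to both rules at once ("see section 4.1 data handling above and" Diagram 2 and Table 3). The figure under "Diagram 2: Safety protocol - For use at inception 3, 6 and 12 months" is not shown in the text available.

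**The concern.** The rule decides when an infant leaves the blinded, assigned dose. Two people following the same protocol, one reading 4.1 and the other Table 3, could treat the same result differently.

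A move to 400 IU/d changes nothing for an infant already assigned 400 IU/d. It lowers the dose only for an infant assigned 1000 IU/d, so each unneeded switch narrows the contrast the trial is built to measure. The infant's dose is then known to family and staff, which sits badly with the aim in Section 3.17 (frequency of analyses) of keeping all staff blinded throughout.

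The PTH case is the most awkward. Trial infants enter with 25(OH)D below 50 nmol/L (Section 3.5). If PTH stays above 60 pg/ml with normal minerals, 4.1 would cut the supplement from 1000 to 400 IU/d. Table 3, on its natural reading, would keep the assigned dose.

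**Working it through.** There is no planned figure to reproduce. The check sets the two rules side by side for a result that is confirmed on repeat and otherwise isolated.

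| Result | Section 4.1 | Table 3 | Comparison |
|---|---|---|---|
| 25(OH)D >225 nmol/L, minerals normal | 24-h repeat, then move | Move at physician's discretion; repeat in 3 months | Stated conflict in action and timing |
| TRP abnormal, plasma normal | 24-h repeat, then move | Repeat in 3 months; unblind if still low | Stated conflict in action and timing |
| Phosphorus persistently <1.0 or >3.0 mmol/L | Move | Urgent referral; no move stated | Different action; move neither ordered nor excluded |
| PTH <10 or >60 pg/ml, minerals normal | Move | Study routine, if the pronoun means the minerals | Conflict on the natural reading |
| Total Ca >2.6 mmol/L alone | Move | Move named for the joint finding; isolated value not addressed | Inferred difference |
| Urine Ca:Cr >2.2 alone | Move | Action named for the joint finding; isolated value not addressed | Inferred difference |
| Ionized Ca outside limits | Move | Unblind; move or other suitable action | Broad agreement |

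**What counts as abnormal.** Table 3 separates normal ranges from action limits. Plasma Ca is normal at 2.2-2.6 mmol/L, but low-side action starts below 2.0. Phosphorus is normal at 1.55-2.65, but action starts below 1.0 or above 3.0. A repeated total Ca of 2.1 lies outside the normal range yet triggers no step in Table 3. Under 4.1, which gives no limits, it could be taken as a reason to switch.

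**Effect on the contrast.** The assigned dose difference is 1000 − 400 = 600 IU/d. If a share p of the 1000 IU/d arm has been switched, and adherence is otherwise full, the mean difference received after the switch is 600 × (1 − p) IU/d. The protocol gives no value for p.

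**Timing.** The sample size rests on lean mass at 3 months (Section 3.11). Only switches triggered by baseline tests can act before that scan. Table 1 schedules PTH, calcium, phosphate and urine Ca:creatinine at baseline, but the Liaison safety assay for 25(OH)D only at 3 and 6 months after screening. The 25(OH)D conflict therefore cannot touch the 3-month result. Switches from the 3- and 6-month tests can affect the 12-month scan.

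**How often 25(OH)D would matter.** Table 3 reports that no infant on 1200 IU/d or less exceeded 225 nmol/L by LC-MS/MS in the previous trial. The Liaison assay may read up to 20% high, so a reading of 225 could be a true value as low as 225 / 1.20 = 187.5 nmol/L. The event should be rare but cannot be taken as impossible.

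**Percentile label.** The plasma Ca row uses a 95th percentile of ionized Ca, and the urine row uses the 97.5th for the same joint criterion. The table lists only the 2.5th and the 97.5th (1.47, 1.46, 1.41 and 1.39 at ≤1, 3, 6 and 12 months). The plasma Ca criterion cannot be applied from the table as written.

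**The case against.** The strongest reply is that 4.1 is a one-line summary. Its preceding clause sends abnormal findings to the study physicians, it gives no limits of its own, and Section 4.2 names it together with Diagram 2 and Table 3. Diagram 2 is the likely home of the decision sequence and cannot be seen. This has weight: the diagram may settle which rule governs, so it cannot be said that the protocol sets no precedence. But no diagram can make an unconditional sentence agree with a row that leaves the move to the physician or waits 3 months. The physician clause under Additional Aspects of Safety Monitoring concerns staying on study after treatment is withdrawn. It does not say which result causes withdrawal.

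The PTH row is open to another reading. Its pronoun could cover all the repeated tests, PTH included. A persistently abnormal PTH would then fall outside the study-routine clause, and 4.1 would not be contradicted. The minerals are the nearer and more natural referent, but with the row unfinished this leg is less secure than 25(OH)D or TRP.

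A reader might infer that Table 3 forbids a move on an isolated high total Ca or urine Ca:creatinine. It does not say so. It names an action for the joint finding and is silent on a confirmed isolated value. For urine Ca:creatinine it gives no stand-alone normal range, so an isolated high value need not count as abnormal at all.

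A reader might also count the scheduled tests at which the rules could differ and take that as a size. Such a count gives opportunities, not expected switches.

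Finally, the plainest conflict, 25(OH)D, concerns what should be a rare event. That is right, and it keeps the point small.

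**Conclusion.** The point stands as a minor inconsistency in the dose-switching rule. The contradiction is explicit for 25(OH)D and TRP. For phosphorus Table 3 states a different action without naming a move. For PTH the contradiction holds if the pronoun means the minerals. For isolated high total Ca and urine Ca:creatinine the difference is inferred from a joint condition. The percentile mismatch is a separate, real slip in a safety threshold.

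Following 4.1 literally would produce open-label switches that Table 3 does not call for, all of the dose reduction falling in the 1000 IU/d arm. The size cannot be estimated from the documents. It is probably small for the 3-month scan, because only baseline tests can act before it.

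A reader might infer that the primary comparison is compromised. The documents do not support that: switched infants are followed and analysed as randomized, so the intent-to-treat comparison stays valid. What is at risk is a narrower contrast and the loss of blinding for the infants concerned. The conclusion assumes that Diagram 2 does not replace the 4.1 sentence with a different rule.

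**What to change.** - Reword the sentence in Section 4.1 so that abnormal results are handled by the analyte-specific limits and actions in Table 3, and confirm that Diagram 2 agrees.
- Have the study physicians complete the PTH row, making clear which tests must be normal and what follows if minerals are abnormal.
- Have them state the action for a confirmed isolated high total Ca or urine Ca:creatinine. The clinical choice for each analyte is theirs.
- Use the tabulated 97.5th ionized Ca percentile in the plasma Ca row, as in the urine Ca:creatinine row.

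The cost is one sentence in 4.1, a few lines and one label in Table 3, and a check of the diagram. No scheduled visits, samples or staff are added.

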#### Additional Aspects of Safety Monitoring.

Should an infant be identified with growth failure, defined as crossing major percentiles a report will be sent to the infant's physician for follow-up. Since there are no standards by which to judge infant lean, fat and bone mass, changes in these will be examined. In any withdrawal of treatment scenario, these infants will continue on study unless advised otherwise by the physician and if treatment withdrawal is warranted, they will be followed as intent-to-treat.

461      Table 1. Summary of study measurements and timing

| Measurement                                   | Screening | Baseline | 3
mo | 6
mo | 12
mo | 24 & 36
mo |
|-----------------------------------------------|-----------|----------|---------|---------|----------|---------------|
| Biochemistry                           |           |          |         |         |          |               |
| Total 25(OH)D by Liaison                      | x         |          | x       | x       |          |               |
| Serum vitamin D metabolites by LC-MS/MS       |           | x        | x       | x       | x        | x             |
| 25(OH)D                                       |           |          |         |         |          |               |
| C-3 alpha epimer of 25(OH)D                   |           |          |         |         |          |               |
| 24,25(OH) 2 D                      |           |          |         |         |          |               |
| 1,25(OH) 2 D                       |           |          |         |         |          |               |
| Parathyroid hormone                           |           | x        | x       | x       | x        | x             |
| Ionized calcium, total Ca and PO 4 |           | x        | x       | x       | x        | x             |
| Urinary calcium:creatinine                    |           | x        | x       | x       | x        |               |
| IGF-1 and IGFBP3                              |           | x        | x       | x       | x        | x             |
| Epigenetic mechanisms                         |           | x        | x       |         |          |               |
| Anthropometry                          |           |          |         |         |          |               |
| Weight                                        | x (chart) | x        | x       | x       | x        | x             |
| Length (height)                               |           | x        | x       | x       | x        | x             |
| Head Circumference                            |           | x        | x       | x       | x        | x             |
| Body composition and bone by DXA              |           | x        | x       | x       | x        | x             |
| Surveyed Information                   |           |          |         |         |          |               |
| Obstetrical record                            | x (chart) |          |         |         |          |               |
| Demographic surveys                           | x         | x        |         |         |          |               |
| Adverse events/any illnesses                  |           | x        | x       | x       | x        | x             |
| Dietary/supplement intake & compliance        |           | x        | x       | x       | x        | x             |
| Sun exposure/skin pigmentation                |           | x        | x       | x       | x        | x             |
| Activity (HAES)                               |           |          |         |         |          | x             |

Abbreviations: DXA: dual-energy x-ray absorptiometry; HAES: habitual activity estimation scale;  
IGF-1: insulin like growth factor-1; IGFBP3: insulin like growth factor binding protein 3; LC-MS/MS:  
liquid chromatography tandem mass spectroscopy.

462  
463  
464  
465  
466  
467  
468  
469  
470  
471  
472  
473  
474  
475  
476  
477

Table 2. Study time-lines (6 year grant October 1, 2015 to September 30, 2021)

| Period             | Activities                                                                                                                                                                                                                                                                                                                                                                                    | Comments                                                                                                                                                                                                                                                                                                                                                                                                                                                                                                                                                                                                                                                                                                                                           |
|--------------------|-----------------------------------------------------------------------------------------------------------------------------------------------------------------------------------------------------------------------------------------------------------------------------------------------------------------------------------------------------------------------------------------------|----------------------------------------------------------------------------------------------------------------------------------------------------------------------------------------------------------------------------------------------------------------------------------------------------------------------------------------------------------------------------------------------------------------------------------------------------------------------------------------------------------------------------------------------------------------------------------------------------------------------------------------------------------------------------------------------------------------------------------------------------|
| July-October 2015  | 
 
Funding notice (July)
 
Steering committee meeting (July)
 
Ethics review (Aug)
 
Students begin program (Sept)
 
Register trial www.clinicaltrials.gov
 
Set up RANDOMIZATION.net
 
Printing of study materials
 
Prepare/receive supplements
 
 | 
All staff are currently available to transfer from other projects.
 
Letter of no objection from Health Canada will be obtained.
 
Euro-Pharm has agreed to provide supplements in kind – see budget page attachments for letter of support.
                                                                                                                                                                                                                                                                                                                                                                                                                                                                                      |
| October 2015-2018  | 
Begin screening recruitment at each hospital's newborn unit (Ethics review in Quebec hospitals is now streamlined so we apply to one site and the others adopt the certificate):
 
 
Ste. Justine Hospital
 
Lakeshore General Hospital
 
McGill University Health Centre (new 2015 Glen site)
 
                      | 
Recruitment is to be overseen by [name]. Study staff and trainees will visit each hospital 5 d a week to recruit for screening. Parent(s) of healthy newborn infants born to generally healthy mothers will be asked if they would like vitamin D status measured as screening for a trial; and if so this would be done using blood taken at the same time as newborn screening. Short demographic and obstetric surveys would be completed. Vitamin D will be measured daily and parents contacted to see if they would like to participate in the trial depending on vitamin D status below 50 nmol/L 25(OH)D or above (reference group). Results of the screening will be given to parents; not thereafter unless safety issues arise.
 |
| October 2015-2018  | Recruitment to trial and begin study sampling, measurements and surveys. Data entry is ongoing as collected.                                                                                                                                                                                                                                                                                  | Trial is held at Mary Emily Clinical Nutrition Research Unit of the School. All aspects conducted at this site as overseen by the PI; and safety monitoring communicated to study physicians by research nurse.                                                                                                                                                                                                                                                                                                                                                                                                                                                                                                                                    |
| March 2016         | Steering Committee meetings every 6 mo from this point.                                                                                                                                                                                                                                                                                                                                       | Meetings mixed format; in person for those local and by joined teleconference for [name] and [name]. All investigators, staff, trainees.                                                                                                                                                                                                                                                                                                                                                                                                                                                                                                                                                                                                           |
| October 2018       | Complete and clean database on screening.                                                                                                                                                                                                                                                                                                                                                     | The screening data is valuable, the data can be written up as a report for presentation at scientific conferences and publishing in peer-review journals (open access).                                                                                                                                                                                                                                                                                                                                                                                                                                                                                                                                                                            |
| January-March 2019 | Epigenetics                                                                                                                                                                                                                                                                                                                                                                                   | Begin analyses using the animal study; then later in year 4 work with baseline and 3 mo buffy coat samples; extraction of DNA and methylation studies. Communicate results as these become available, scientific meetings and peer-review journals.                                                                                                                                                                                                                                                                                                                                                                                                                                                                                                |
| October 2019-      | Complete biochemistry. Complete and clean database on trial.                                                                                                                                                                                                                                                                                                                                  | Begin analysis of data and communicate results. Publish in peer-review journals (open-access format).                                                                                                                                                                                                                                                                                                                                                                                                                                                                                                                                                                                                                                              |
| October 2017-2021  | Complete 2-3 y data points including sampling, biochemical analyses, surveyed information etc. Build and clean database, reporting.                                                                                                                                                                                                                                                           | Communicate results, scientific meetings and peer-review journals.                                                                                                                                                                                                                                                                                                                                                                                                                                                                                                                                                                                                                                                                                 |

Table 3. Normative values and threshold values used in safety monitoring

|                                             |                                                                                                                                                                                                                                                                                                                                                                                                                                                                                                                                                                                                                                  |       |      |      |       |
|---------------------------------------------|----------------------------------------------------------------------------------------------------------------------------------------------------------------------------------------------------------------------------------------------------------------------------------------------------------------------------------------------------------------------------------------------------------------------------------------------------------------------------------------------------------------------------------------------------------------------------------------------------------------------------------|-------|------|------|-------|
| 25(OH)D                                     | Safe range <225 nmol/L according to Canadian Paediatric Society (CPS) and using our in-house Liaison total 25(OH)D (Diasorin) to enable 24 h assessments. This assay may overestimate by up to 20% (1) and thus we have used the CPS guidelines here for safety assessments only. None of the infants in the previous trial (2, 3) had values above this if vitamin D dosage was ≤1200 IU/d and using LC-MS/MS analyses. If value exceeds this limit then review plasma and urine mineral concentrations and consider moving to standard of care based on physician assessment; if these are normal, then repeat sample in 3 mo. |       |      |      |       |
| PTH                                         | Normal range 10-60 pg/ml. If value <10 or >60, PTH to be repeated with plasma and urine minerals. As long as these are within the normal range, follow as per study routine. If any mineral concentrations are abnormal as per the criteria defined below.                                                                                                                                                                                                                                                                                                                                                                       |       |      |      |       |
| Plasma Ca                                   | Normal range 2.2 –2.6 mmol/L. If value <2.0 or >2.6, repeat sample and include ionized Ca, P, and urine minerals. If total Ca <2.0 and ionized Ca <1.0, break study code. If total Ca >2.6 and ionized Ca > age specific 95% percentile and urine Ca:Cr >2.2, safety officers unblind the infant, move to standard of care and send for urgent endocrine assessment.                                                                                                                                                                                                                                                             |       |      |      |       |
| Ionized Ca                                  | Normal range for age using data from our previous trial (2, 3) which has been adopted by children's hospitals. If value is outside of 2.5 th to 97.5 th percentile range (see table below), sample to be repeated within 24 h. If repeated values are abnormal, safety officers to unblind that infant, move to standard of care or other appropriate action and potentially send for urgent endocrine assessment.                                                                                                                                                                                         |       |      |      |       |
